**Figure 2 figure2:**

State transition diagram for competing risks multistate model for a retrospective cohort of adults with chronic liver disease (CLD) in England between January 1, 2012, and December 31, 2022, evaluating hepatitis A (Hep A) vaccination with 1 and 2 doses as outcomes and death as a competing risk represented as an absorbing state.

A multistate survival model will be fitted to estimate the transition probabilities between the 4 identified study states (Figure 2). The states are (1) diagnosis of CLD, (2) first dose of Hep A vaccination, (3) death, and (4) second dose of Hep A vaccination. The outcome of interest is the Hep A vaccination. Therefore, the state of a second dose of Hep A vaccination is a censored state, with no further transitions to death; the moment a patient receives 2 doses of Hep A vaccination, the follow-up ends. Death is an absorbing state, with no further transitions allowed. Death is included as a competing risk for vaccination, not as an outcome. This means that when calculating the transition probabilities to vaccination, we adjust for when a person is not vaccinated because of death before vaccination rather than for any other predictors of nonvaccination.

Patients lost to follow-up will be right censored and evaluated accordingly as per the likelihood function of the “msm” R package [30].

Multistate probabilities are based on the same assumptions as a Markov process:

The health states considered in the model are thorough and mutually exclusive.The probability to move from one health state to following states only depends on (is conditioned on) the health state of the individual at transition time (memoryless process).Transition probabilities are steady over time.

The state transition probabilities will be estimated conditional on the study risk factors. Study risk factors include (1) etiology of CLD (eg, ALD, CH-B, CH-C, and NAFLD); (2) sociodemographic characteristics (eg, age, sex, ethnicity, deprivation, obesity, smoking, and alcohol consumption); (3) CLD complications (eg, bile duct and colon cancers, renal disease, ascites, liver failure and transplant, and cardiometabolic disease); and (4) comorbidities (eg, CMMS, bile duct and colon cancers, at least 3 doses of COVID-19 vaccine, and flu vaccination).

The multistate model will be estimated using the “msm” (version 1.6.9) package in R [31].

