**Methods:**

We will conduct a retrospective cohort study with data from the Primary Care Sentinel Cohort of the Oxford-Royal College of General Practitioners Clinical Informatics Digital Hub database, which is nationally representative of the English population. We will include people aged 18 years and older who have been registered in general practices in the Research and Surveillance Centre network and have a record of CLD between January 1, 2012, and December 31, 2022, including those with alcohol-related liver disease, chronic hepatitis B, chronic hepatitis C, nonalcohol fatty liver disease, Wilson disease, hemochromatosis, and autoimmune hepatitis. We will carefully curate variables using the Systematized Nomenclature of Medicine Clinical Terms. We will report the sociodemographic characteristics of those who are vaccinated. These include age, gender, ethnicity, population density, region, socioeconomic status (measured using the index of multiple deprivation), obesity, alcohol consumption, and smoking. Hepatitis A vaccination coverage for 1 and 2 doses will be calculated using an estimate of the CLD population as the denominator. We will analyze the baseline characteristics using descriptive statistics, including measures of dispersion. Pairwise comparisons of case-mix characteristics, comorbidities, and complications will be reported according to vaccination status. A multistate survival model will be fitted to estimate the transition probabilities among four states: (1) diagnosed with CLD, (2) first dose of hepatitis A vaccination, (3) second dose of hepatitis A vaccination, and (4) death. This will identify any potential disparities in how people with CLD get vaccinated.

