## Discussion

### Overview

This study will inform on the state of preventive Hep A vaccination for people with CLD in a representative primary care sentinel network in England. From a total of 7.4 million patients in the RSC network, we will report on the sociodemographic and clinical characteristics of people with CLD with and without Hep A vaccination, for 1 and 2 doses.

The multistate model, adjusted for study risk factors, will identify those associated with having the vaccination. This will inform on the individual characteristics that are associated with an immunization, informing on the subgroups that could benefit from higher engagement with preventive primary care. Any disparities identified could be used to target clinical and public health interventions to improve vaccination coverage in this at-risk group.

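### Transition probabilities described as adjusting for death still contain the death rate, so disparities in vaccination should be judged on intensity (hazard) ratios from the same model

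*Protocol article*

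**What the plan says.** The model is described in the protocol article under Methods, Statistical Analysis, in the subsection on predictors of 1 and 2 doses (text at Figure 2).

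- **Output.** "A multistate survival model will be fitted to estimate the transition probabilities between the 4 identified study states". The states are CLD diagnosis, first dose, second dose and death.
- **Covariates.** "The state transition probabilities will be estimated conditional on the study risk factors". The risk factors include etiology, sociodemographic characteristics, comorbidities and complications, the last listed as "bile duct and colon cancers, renal disease, ascites, liver failure and transplant, and cardiometabolic disease".
- **Death.** "Death is included as a competing risk for vaccination, not as an outcome". The article then explains that "when calculating the transition probabilities to vaccination, we adjust for when a person is not vaccinated because of death before vaccination", and contrasts this with adjusting for other reasons for non-vaccination.
- **Time.** "Transition probabilities are steady over time".
- **Use.** In the Abstract (Methods), directly after the transition probabilities are named: "This will identify any potential disparities in how people with CLD get vaccinated". In the Discussion (Overview), the model is to identify factors associated with vaccination, "informing on the subgroups that could benefit from higher engagement with preventive primary care".

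The article does not name transition intensities, cause-specific hazards or hazard ratios as the measure on which predictors will be judged. The Limitations section refers only to multivariate time-to-event modeling within the multistate model.

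**The concern.** Objective 2 asks which people with CLD are missed for vaccination. Two processes determine whether a patient reaches a vaccinated state: how fast patients are vaccinated while alive, and how fast they die first. A transition probability combines the two. Saying that it adjusts for death invites the reader to think that mortality has been taken out, when treating death as a competing risk builds it in.

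If groups are compared on these probabilities, a group with high mortality can appear under-vaccinated although its living members are offered and given vaccine at the same rate as everyone else. Several listed risk factors plausibly carry high mortality. The Discussion intends to use the results to choose subgroups for more engagement, so some could be chosen because their members die sooner and not because primary care misses them.

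**Working it through.** **Inputs.** From the article: the four states, death as an absorbing competing risk, and steady transitions over time (taken here as constant intensities). It also gives a window of January 1, 2012 to December 31, 2022, and a coverage range of 10% to 50% (Study Size). Assumed: all vaccination and death rates, because the article gives no mortality for its cohort.

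**Formula.** Let L be the first-dose intensity and M the death intensity before dose 1, both per year. Under the article's own model the cumulative probability of a first dose by time t is

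P(t) = L/(L+M) × [1 − exp(−(L+M)t)].

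M appears in both factors. For fixed L, P(t) falls as M rises.

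**Main illustration.** L = 0.05 in both groups, so the vaccination rate ratio while alive is 1.00. M = 0.02 versus 0.15.

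| Horizon | M = 0.02 | M = 0.15 |
|---|---|---|
| 1 year | (0.05/0.07)(1 − e^−0.07) = 4.8% | (0.05/0.20)(1 − e^−0.20) = 4.5% |
| 5 years | (0.05/0.07)(1 − e^−0.35) = 21.1% | (0.05/0.20)(1 − e^−1.00) = 15.8% |
| 10 years | (0.05/0.07)(1 − e^−0.70) = 36.0% | (0.05/0.20)(1 − e^−2.00) = 21.6% |

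The gap is about 0.3, 5.3 and 14 percentage points in turn.

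**Milder contrasts.** Set L so that 10-year coverage without deaths would be 30%: L = −ln(0.70)/10 = 0.0357.

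| Horizon | M = 0.01 | M = 0.02 | M = 0.10 |
|---|---|---|---|
| 1 year | 3.49% | 3.47% | 3.34% |
| 5 years | 15.9% | 15.6% | 13.0% |
| 10 years | 28.6% | 27.4% | 19.5% |

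For M = 0.10 versus 0.01 the 10-year probability ratio is 0.68. It is 0.67 or 0.70 if coverage without deaths is set to 10% or 50%. The M = 0.10 group would have to be vaccinated 1.59 times as fast while alive to show the same 10-year probability as the M = 0.01 group.

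**Check on the hazard scale.** A simulation of the last contrast (M = 0.01 versus 0.10, 400,000 patients per group) gave a 10-year probability ratio of 0.68 but a ratio of vaccination rates per person-year alive of 1.00. The apparent disparity disappears on the intensity scale.

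**Realistic horizon.** If entry is at first diagnosis within the window, only patients diagnosed by the end of 2012 can be followed for 10 years. With entry spread evenly over the 11 years (an assumption), mean potential follow-up is 11/2 = 5.5 years before any loss or death. The 5-year row is then nearer to what the data can show directly.

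**Scale.** These are cumulative probabilities of ever receiving a first dose. The model's probability of being in the first-dose state at time t is a different quantity, lowered further by second doses and by deaths after dose 1.

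**The case against.** The strongest reply is that the article is a condensed account and need not list every reported measure. The msm package places covariates on the intensities, so hazard ratios come from the planned fit anyway. The Discussion and Limitations sections are compatible with reading covariate effects from the fitted model. Read whole, the sentence on adjustment can mean only that deaths before vaccination are taken into account, which a competing-risk probability does. And the share of a group vaccinated before death is a legitimate quantity in a coverage study.

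Much of this stands. The absence of hazard ratios from the article would not be a finding by itself, and reporting the probabilities is not an error. What remains is that the article names covariate-conditional probabilities as its output and attributes to them an adjustment for death that can be read as removing mortality. The Abstract then links them directly to disparities.

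The objection on size also stands. The mortality contrast is assumed and held constant. Because the model conditions on complications and comorbidity, the contrast that matters for, say, deprivation is the residual one. The second-dose step adds little once the 12-month base-case window is applied. With an assumed dose-2 rate of 0.50 per year, the probability of dose 2 within a year of dose 1 is (0.50/0.52)(1 − e^−0.52) = 39.0% versus (0.50/0.65)(1 − e^−0.65) = 36.8%.

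**Conclusion.** The point holds as a matter of wording and choice of measure. The probabilities reflect both vaccination and death, and the plan should not describe them as adjusted for death in a way that lets disparities be read from them without qualification.

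A reader might go further and infer that the planned analysis will produce false disparities of 10 points or more, or that every listed factor will emerge as a predictor through mortality alone. The documents do not support this. They give no subgroup mortality, and they do not say that groups will be ranked on 10-year probabilities. The effect is slight over 1 year, or when death rates differ only between 1% and 2% per year. It becomes material over 5 to 10 years when one group's death rate is around 10% to 15% per year. The 10-year figures of 36.0% versus 21.6% are an upper illustration of the main scenario, since few patients will have that much follow-up.

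The direction of the effect rests only on the article's own Markov model. Its size rests on the assumed rates.

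**What to change.** 1. State that predictors and disparities for objective 2 are judged on covariate intensity (hazard) ratios with 95% CIs, for CLD diagnosis to dose 1 and for dose 1 to dose 2, from the planned msm fit.
2. Keep the transition probabilities as absolute descriptions at stated horizons, and show them next to the death-intensity ratios so that the reader can see how much of a difference reflects mortality.
3. Replace the sentence on adjusting for death with one saying that the probabilities reflect both vaccination and death before vaccination.

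No new data, model or fit is needed. The cost is a change of wording and slightly longer results tables.

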## Introduction

### Overview

Hepatitis A (Hep A) is a viral infection of the liver caused by the hepatitis A virus (HAV). HAV is transmitted through the fecal-oral route, mainly by exposure to contaminated water sources. Hep A outbreaks are uncommon in the United Kingdom, and most people manifest mild to moderate symptoms that tend to resolve, without sequelae, within several months. In high-risk groups, however, such as people with an underlying chronic liver disease (CLD), a superimposed acute infection with HAV can be severe, potentially requiring hospitalization and carrying a higher risk of death. According to the World Health Organization, approximately 100 million Hep A infections occur globally per year, resulting in 15,000 to 30,000 deaths per year [1]. Of these, the number of people with a preexisting CLD diagnosis remains unclear.

CLD largely results from the progressive destruction and regeneration of hepatocytes, leading to fibrosis and cirrhosis, and has a range of etiologies. The most common causes of CLD include alcohol-related liver disease (ALD), chronic hepatitis B (CH-B) infection, chronic hepatitis C (CH-C) infection, and nonalcoholic fatty liver disease (NAFLD), the latter being associated with metabolic syndrome and obesity [2,3]. Deaths in the United Kingdom from CLD have increased annually for the past decade, peaking at 20.6 per 100,000 population in 2020 [4,5], and are expected to surpass the numbers of premature deaths from coronary heart disease [3], CLD-related hospitalizations in the United Kingdom have increased by half, contributing to the £2.1 (US $2.62) billion per year currently spent on treating liver disease [4,6].

The UK’s public health body, the Health Security Agency, and the national guideline body, the National Institute for Health and Care Excellence, recommend preexposure Hep A vaccination to all people with CLD, regardless of the cause [7,8]. The Hep A vaccine series consists of 2 doses, with the second dose at least 6 months after the first.

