### Objectives

The objectives of this study are as follows:

To report yearly Hep A vaccination coverage in people with CLD by:sociodemographic characteristics (eg, age, sex, ethnicity, deprivation, BMI category, smoking status, and alcohol consumption)etiology of CLD (eg, ALD, CH-B, CH-C, and NAFLD).CLD complications (eg, renal disease, ascites, liver failure and transplant, and other cardiometabolic diseases, including diabetes and heart disease)comorbidities and exposures (eg, Cambridge Multimorbidity Score [CMMS], bile duct and colon cancers, at least three doses of COVID-19 vaccine, and flu vaccination).To report the predictors of 1 and 2 doses of Hep A vaccination in people with CLD.

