#### Reporting Predictors of 1 and 2 Doses of Hep A Vaccination in People With CLD

##### Overview

A multistate model will be used on a retrospective cohort of individuals identified in the ORCHID diagnosed with CLD. People enter the study on the first diagnosis of CLD, and we will model the transition probabilities between the identified states: diagnosed with CLD, first dose of Hep A vaccination, second dose of Hep A vaccination, and death (Figure 2).

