### Limitations

Selection and misclassification biases can be associated with the retrospective study design. However, this can be mitigated by the availability of reliable records in the database. Similarly, the retrospective study design has a limitation to establishing causal relationships due to the temporality and lack of randomization. However, retrospective associations can be a timely source of epidemiological data to guide further research.

There exists potential confounding due to case-mix characteristics, which will be mitigated through multivariate time-to-event modeling in the multistate model.

Large general practice databases are susceptible to coding errors or inaccuracies that may be associated with ascertainment and misclassification biases. This is mitigated by the large representative sample of UK practices within the RSC network, which controls for random error and variation on these parameters [18].

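### The predictor model fixes time-constant vaccination rates; if the first-dose rate in fact changes over time, hazard ratios for predictors tied to early death or to diagnosis date will be distorted

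*Protocol article*

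**What the plan says.** Under Methods, Statistical Analysis, in the section on predictors of 1 and 2 doses, the article sets the clock at diagnosis: "People enter the study on the first diagnosis of CLD, and we will model the transition probabilities between the identified states". After the Figure 2 caption it lists the model's assumptions. One is that the process is memoryless. Another is "Transition probabilities are steady over time". It continues: "The state transition probabilities will be estimated conditional on the study risk factors". Four groups of risk factors follow: etiology, sociodemographic characteristics, complications and comorbidities. None is a time variable. The Covariates section takes sociodemographic variables, including age, near the diagnosis date, so age does not serve as a clock.

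The Sensitivity Analysis section varies the window for dose 2 and allows a complete-case analysis. Neither relaxes the constant-rate assumption. The first objective, by contrast, is by year: "To report yearly Hep A vaccination coverage in people with CLD by". The Limitations section relies on the same model for adjustment: "There exists potential confounding due to case-mix characteristics, which will be mitigated through multivariate time-to-event modeling in the multistate model".

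**The concern.** With dated transitions and a constant intensity, the first-dose rate in a group is simply first doses divided by person-years at risk, pooled over all follow-up from 2012 to 2022. Suppose the rate is higher soon after diagnosis, which is plausible because the vaccine is recommended on account of CLD. Members of a group that dies early, or that tends to be diagnosed late in the window, then spend a larger share of their observed time in the high-rate period. The group shows a raised HR even if its members are vaccinated at exactly the same rate as everyone else at each point after diagnosis. Adjusting for the group does not help, because the group's own coefficient is the one distorted.

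The second objective is to find disparities, and the Discussion intends them to guide interventions. An artefactual HR above 1 for ascites or liver failure could hide under-vaccination there. An artefact in either direction could be reported as a disparity.

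**Working it through.** **The plan's size figure.** Study Size gives 7.4 million patients and an incidence of 20.7/100,000. The product is 7,400,000 × 20.7/100,000 = 1,531.8 a year, not the stated 1656; 8,000,000 × 20.7/100,000 = 1,656. I use 1,532 × 11 years = 16,852. The choice affects the false-positive rates, not the HRs.

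**Assumed inputs (none is in the documents).** Entry is uniform over 11 years and follow-up ends with 2022. The first-dose rate is common to both groups: e per year in year 1 after diagnosis, l per year afterwards. Mortality in group g is μ_g. The exposed group is 20% of the cohort. The true HR is 1.

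**Formula.** The fraction still at risk t years after diagnosis is y_g(t) = exp(−∫(λ + μ_g)) × (1 − t/11). Let w_g be the share of group person-time that falls in year 1. The constant model then estimates rate_g = l + (e − l) × w_g, and its HR is the ratio of these rates.

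**One case in full.** Take e = 0.10, l = 0.02, mortality 0.15 v 0.03.
- Exposed: 0.846 + 2.162 = 3.009 person-years each (rounded), w = 0.281, rate = 0.02 + 0.08 × 0.2813 = 0.0425.
- Unexposed: 0.896 + 3.402 = 4.298, w = 0.208, rate = 0.02 + 0.08 × 0.2085 = 0.0367.
- HR = 0.04250/0.03668 = 1.16.
- Expected first doses: 431 and 2,125. SE of log HR = √(1/431 + 1/2,125) = 0.053; z = 0.147/0.053 = 2.79. Chance of P<.05 = Φ(2.79 − 1.96) = 80%.

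**Other cases, same method.**

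| Assumption | HR, constant model | False positives |
|---|---|---|
| 0.20 then 0.04; mortality 0.15 v 0.03 | 1.16 | 96% |
| 0.06 then 0.03; mortality 0.15 v 0.03 | 1.06 | 18% |
| 0.10 then 0.02; mortality 0.05 v 0.03 | 1.03 | 8% |
| 0.05 throughout; mortality 0.15 v 0.03 | 1.00 | 5% |
| 0.20 then 0.04; equal mortality, etiology share rising 20% to 50% | 1.08 | 75% |
| 0.08 falling 10% per calendar year; same rising share | 0.94 | 31% |
| 0.08 falling 10% per calendar year; mortality 0.15 v 0.03 | 1.04 | not computed |

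A second set of assumptions (mortality 0.02 v 0.15, two equal groups) gave HRs of 1.07, 1.17 and 1.25 for rates of 0.10/0.05, 0.15/0.03 and 0.20/0.02.

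**With time terms.** In simulations, time bands returned the HR to about 1.00 with false-positive rates of 3% to 6%. Splitting by time since diagnosis and calendar year together returned 1.000 in the numerical cases of the second set. The bands there matched the assumed change points, so real data could leave some residual distortion.

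**Probabilities.** For the unexposed group in the full case, the true first-dose probability at 1 year is 0.10/0.13 × (1 − e^(−0.13)) = 9.4%. The constant model gives 0.0367/0.0667 × (1 − e^(−0.0667)) = 3.5%. The two nearly agree at 5 years (15.7% true, 15.6% fitted) and have separated again by 10 years (22.1% true, 26.8% fitted).

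**The case against.** The strongest reply is that the size is built from assumptions. The large values combine a fivefold fall in the vaccination rate with a fivefold mortality contrast, and the high false-positive rates partly reflect a cohort of about 17,000. That stands: the point is conditional, and the HR is a better guide to the damage than the false-positive rate.

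Second, the plan adjusts jointly for many factors, whereas the cases above have one. In a simulation with alcohol-related liver disease and ascites together, where ascites was assumed to carry most of the excess mortality, the HR for the etiology fell from 1.06 to 1.02 (7% false positives). Ascites itself stayed at 1.17 (69%). Joint adjustment therefore narrows the problem to direct mortality markers. It does not address the separate route through diagnosis date.

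Third, the article is condensed and its risk-factor items are examples. But the constant rate is stated as an assumption, none of the four groups is temporal, and adding a time term would contradict the text.

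Three stronger readings are tempting and unsupported:
- A reader might infer that the Introduction contradicts the assumption, since it says "Deaths in the United Kingdom from CLD have increased annually for the past decade, peaking at 20.6 per 100,000 population in 2020". That rate is per head of population and can rise through prevalence alone. A misspecified death rate also does not bias the first-dose HR, because the likelihood separates by transition; it affects only the transition probabilities.
- A reader might infer that yearly reporting shows the authors expect change. It allows for change and no more.
- A reader might infer that falling uptake over calendar time makes the sickest groups look worse. It makes them look slightly better (HR 1.04), because their person-time lies earlier. Late-diagnosed groups are the ones that look worse.

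**Conclusion.** The concern holds in conditional form. The article fixes constant intensities and provides no time term, check or sensitivity analysis that would relax them. If the first-dose rate changes with time, HRs are distorted for strong mortality markers and for predictors tied to diagnosis date. A fall after diagnosis makes both look better vaccinated than they are. A calendar fall makes late-diagnosed groups look worse.

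Under the assumed rates, the distortion is HR 1.06 to 1.16 for a fivefold mortality contrast, about 1.08 for a strongly rising etiology, and about 0.94 for that etiology under a 10% yearly fall. It is about 1.03 for a weak mortality contrast and absent if the rate is constant. Predictors unrelated to survival or diagnosis date are largely unaffected. First-dose probabilities are misstated at most horizons, chiefly early ones, though not at every one, since the fitted and true curves cross. This should be changed before analysis; it does not invalidate the study.

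**What to change.** For the transition from CLD diagnosis to first dose, replace the steady-rate assumption with piecewise-constant baseline intensities by time since diagnosis, with at least a split at 1 year. Do the same for diagnosis to death, for the sake of the transition probabilities. Add calendar period as a time-varying covariate on these transitions. The msm package already named in the plan has a piecewise-constant option. Report predictor HRs, and transition probabilities at stated horizons, from this model. Keep the constant-intensity model as a comparison, so that readers can see whether the assumption mattered. The exact bands are for the analysts to prespecify.

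The cost is wording in the analysis section, splitting each record at the band and period boundaries, a few extra parameters per transition and a longer run time. The dates needed are those the model already uses.

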### Variables

#### Overview

The study population is those with CLD as an index condition, as defined in the inclusion criteria. The variables will be curated for the identification of CLD-related codes in the computerized medical records of adults registered in the RSC network (Multimedia Appendix 1).

Comparisons will be conducted between population subgroups with different CLD etiologies, sociodemographic characteristics, complications, and comorbidity profiles.

The outcome of the first objective will be the coverage rates of Hep A vaccination among those with CLD.

For the second objective, we will explore significant independent predictors of the following outcomes among those with CLD: (1) one dose of Hep A vaccination and (2) two doses of Hep A vaccination.

Hep A vaccination, as defined by the UK vaccination scheme, includes an initial 0.5 mL for 1 dose, followed by a booster dose of 0.5 mL after 6-12 months. The booster dose may be delayed by up to 3 years if not given after the recommended interval following the primary dose [8]. For this study, we will report boosters administered within 12 months of the first dose for the base case analysis and 3 years from the first dose for a sensitivity analysis. Hep A vaccination in the United Kingdom is available as a monovalent vaccine, as a combined Hep A and hepatitis B vaccine, and as a Hep A and typhoid vaccine [7]. We will consider any Hep A vaccination type as an outcome.

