##### Sensitivity Analysis

We will estimate 2 multistate models by varying the definition of Hep A dose 2. In the first model, the second dose must be administered within 1 year of the first dose; in the second model, dose 2 may occur within 3 years of the first administered dose. A 3-year time window between vaccinations is likely to exclude those who have been recently vaccinated. Hence the need for such a sensitivity analysis. A complete-case analysis to assess any differences due to missing data can be conducted after assessing the missingness of the descriptive data.

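### A constant, memoryless intensity cannot describe a second dose due 6-12 months after the first and counted only inside a window, so the dose-2 probabilities will be wrong

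*Protocol article*

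**What the plan says.** In the multistate model section of the protocol article (text with Figure 2), two assumptions are stated. A move between states "only depends on (is conditioned on) the health state of the individual at transition time (memoryless process"), and "Transition probabilities are steady over time". The model is to be fitted in the R package msm. Follow-up ends at dose 2, and loss to follow-up is right-censored.

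The vaccine schedule is given twice. The Introduction describes a two-dose series "with the second dose at least 6 months after the first". The Variables overview describes a first dose "followed by a booster dose of 0.5 mL after 6-12 months", with a possible delay of up to 3 years.

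The outcome is windowed. Under Sensitivity Analysis, in the first model "the second dose must be administered within 1 year of the first dose"; the second model allows 3 years. These two models differ only in the window. Both keep the constant-probability assumption.

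**The concern.** The schedule and the outcome definition make the chance of dose 2 a function of time since dose 1. The two Markov assumptions rule out exactly that dependence. This is not a detail left for a later document, because the article itself fixes both assumptions.

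Transition probabilities are the model's declared output, and predictors of two doses are half of the second objective. If the dose 1 to dose 2 intensity is misspecified, the reported probability of completing the course is wrong. Differences between subgroups may also partly reflect how long people were followed rather than how they were vaccinated.

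**Working it through.** **No figure to reproduce.** The article gives no rate for the dose 1 to dose 2 transition. The inputs below are assumptions, except for the schedule, the windows and the 2012-2022 span (up to 11 years).

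**Assumed inputs.** Among people with dose 1, a share p = 35% or 60% would receive dose 2, spread evenly over 6-12 months. Death is 3% per year. Follow-up after dose 1 is uniform over 0-11 years.

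**Formulas.** With exactly observed times, the constant-intensity estimate is λ = (dose-2 events) / (person-years after dose 1). With death rate μ as a competing exit, the predicted probability is P(t) = λ/(λ+μ) × [1 − exp(−(λ+μ)t)].

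**Hand check, ignoring death and early censoring.** Completers contribute 0.75 years on average. The others contribute 1 + m years, where m is the time kept at risk after a 12-month window. So λ = p / [0.75p + (1−p)(1+m)].

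- p = 0.60, m = 4: 0.60 / (0.45 + 2.00) = 0.245 per year, and 1 − exp(−0.245) = 21.7% at 12 months, against 60%.
- p = 0.60, m = 0 (censored at 12 months): 0.60 / (0.45 + 0.40) = 0.706, giving 50.6% against 60%.
- p = 0.35, m = 4: 0.35 / (0.2625 + 3.25) = 0.0996, giving 9.5% against 35%.
- p = 0.35, m = 0: 0.35 / (0.2625 + 0.65) = 0.384, giving 31.9% against 35%.

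**Simulation with death, 12-month window.**

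| p | Time after window | λ per year | Predicted, 6 months | Predicted, 12 months | True, 6 / 12 months |
|---|---|---|---|---|---|
| 35% | kept at risk | 0.092 | 4.5% | 8.7% | 0% / 34.2% |
| 35% | censored | 0.370 | 16.8% | 30.5% | 0% / 34.2% |
| 60% | kept at risk | 0.227 | 10.7% | 20.0% | 0% / 58.7% |
| 60% | censored | 0.679 | 28.6% | 48.6% | 0% / 58.7% |

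When people are kept at risk, the error changes sign later. For p = 60% the fitted curve crosses the truth at a little over 4 years and reaches 63.9% at 5 years, against 58.7%.

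**Three-year window.** Take 35% at 6-12 months plus 10% at 12-36 months, with follow-up of 0-10 years. Predicted at 12 months: 12.4% (kept) or 19.6% (censored), against 34.2%. At 36 months: 31.8% or 46.7%, against 43.6%.

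**Predictor effects, 12-month window, no true difference in dose-2 behaviour (true ratio 1).**

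| Contrast | Kept at risk | Censored at window |
|---|---|---|
| Death 5% v 3% per year | 1.04-1.05 | 0.99-1.00 |
| Death 15% v 3% per year | 1.24-1.29 | 0.96-0.97 |
| Death 30% v 3% per year | 1.48-1.61 | 0.92 |
| Recent v early diagnosis (1-5 v 6-10 years of follow-up) | 2.07-2.31 | 1.00 |
| Predictor unrelated to follow-up | 1.00 | 1.00 |

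The ranges run over p = 35% and 60%. The last row was run with p = 35% and 65% and follow-up of 0-10 years.

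**A real effect.** With a true hazard ratio of 2 and equal follow-up (p = 35% and 50%, a further 10% at 12-36 months, follow-up 0-10 years), the 12-month model gives 2.27-2.39 if people are kept at risk and 1.66-1.78 if censored. With the 3-year window it gives 2.30-2.39 or 2.01-2.06.

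**Check of the remedy.** Piecewise-constant intensities in time since dose 1, with cuts at 6, 8, 10 and 12 months, return 0% at 6 months and 34.2% at 12 months for p = 35%. True ratios of 1 under unequal follow-up or unequal mortality come back as 1.00 and 0.99, and a true ratio of 2 as 1.99.

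**The case against.** Several limits on the point are fair and stand.

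- **Predictor effects are not all wrong.** A reader might infer that every dose-2 predictor will be misestimated. A null predictor unrelated to follow-up stays null. The false associations with mortality or diagnosis date need people to stay at risk after the window closes. The article does not say whether they do, and a fuller plan could settle it. Censoring at the window largely removes them and slightly reverses the mortality one.
- **The sizes rest on inputs not in the article.** The mortality effect is small for modest differences. With shorter follow-up after dose 1, death of 15% v 3% gives only 1.05-1.08 (0-5 years) or 1.00-1.01 (0-3 years), even with people kept at risk.
- **No minimum interval is set for counting dose 2.** Some doses before 6 months could count, which softens the misfit without removing it.
- **The first transition is not implicated.** The schedule argument says nothing about diagnosis to dose 1, so one-dose predictors are not shown to be biased.

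Two stronger readings are tempting but unsupported. One is that constant probabilities contradict the aim "To report yearly Hep A vaccination coverage in people with CLD". That coverage is a separate numerator-over-denominator calculation and does not use this model. The other is that, because "the state of a second dose of Hep A vaccination is a censored state", the outcome would be lost. The same sentence explains that no further transition follows and that follow-up ends there, so in function it is a terminal event. The term is loose, but nothing shows that dose 2 would be coded as an unknown state.

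What the objection does not reach is the probability error. In the 12-month base case it is present whether people are kept at risk or censored.

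**Conclusion.** The point holds for the dose 1 to dose 2 transition. The stated assumptions conflict with the article's own schedule and counting windows, and following them gives wrong dose-2 probabilities. Under the assumed completion of 35-60%, the 12-month probability is predicted at about 9-20% (kept at risk) or 30-49% (censored), against 34-59%. At 6 months the model predicts between 4.5% and 28.6% where the truth under these inputs is zero.

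The bias in predictor effects is conditional. If people stay at risk after the window, factors tied to survival or diagnosis date acquire false ratios: about 1.04-1.6 for death of 5-30% versus 3% per year, and about 2.1-2.3 for recent versus early diagnosis. If they are censored at the window, these largely disappear, but a true hazard ratio of 2 is pulled down to 1.66-1.78 in the base case. The direction of the conflict follows from the text alone; only the sizes depend on the assumed inputs.

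**What to change.** Change the model specification before it is fitted:

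1. Drop the constant-probability assumption for the transitions out of dose 1 (to dose 2 and to death). Let them depend on time since dose 1. Either use clock-reset (semi-Markov) transition-specific models, or piecewise-constant intensities with cuts at 6 and 12 months, plus 36 months for the 3-year model. Extra cuts between 6 and 12 months follow the curve more closely.
2. State that the dose-2 risk set ends when the 12-month or 36-month window closes, so that people who can no longer have the counted event add no dose-2 person-time.
3. Describe second dose as a terminal event state, and declare transition times as exactly observed if msm is kept.

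The cost is new wording in the analysis section and somewhat more analysis work. Dose dates are already needed to apply the windows, so no new data are required. This point does not call for a change to the diagnosis to dose 1 transition.
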